# Adjuvant nonavalent HPV vaccination in women treated for vulvar HSIL, a randomized placebo-controlled trial; VulVaccin study protocol

**DOI:** 10.1186/s12885-025-14275-w

**Published:** 2025-05-20

**Keywords:** Vulvar neoplasms, Vulvar high-grade squamous intraepithelial lesion, Papillomavirus vaccines, Adjuvant HPV vaccination, Vulvar HSIL treatment, Vulvar cancer

## Abstract

**Background:**

Each year, 45,000 women worldwide develop vulvar cancer, often occurred from vulvar high-grade squamous intraepithelial lesions (vHSIL), a precancerous stage associated with high- risk human papillomavirus (HPV). Recurrent vHSIL, experienced by over 30% of patients despite treatment, conducting in significant physical and psychosocial challenges. With no established method to reduce recurrence, our study investigates the potential of adjuvant HPV vaccination during treatment. We aim to determine whether nonavalent HPV vaccination can effectively prevent vHSIL recurrence in women treated for vulvar HSIL.

**Methods:**

This is a randomized, double-blind, placebo-controlled study protocol involving 498 women diagnosed with vHSIL. Participants will be randomized to receive either the nonavalent HPV vaccine or a placebo in addition to standard treatment. The primary outcome is the recurrence of vHSIL within 24 months following treatment. Secondary endpoints are treatment effectiveness, immune response, cost-effectiveness, and quality of life. Long-term follow-up examines vaccine effect after 5 and 10 years, along with the occurrence of vulvar malignancies. Relative risk between vaccinated and placebo groups will be evaluated, employing intention-to-treat principles.

**Discussion:**

This study is designed to investigate the potential benefits of HPV vaccination in managing vHSIL. Results from the trial will provide evidence on the vaccine’s impact on recurrence rates, treatment outcomes, and long-term prevention of vulvar malignancies.

**Trial registration:**

ClinicalTrials.gov. Identifier: NCT06052696. Registered 12 January 2023, https://clinicaltrials.gov/study/NCT06052696.

## Background

Annually, approximately 45,240 women globally are affected by vulvar carcinoma, with a yearly mortality of 15.000 [1]. Around one-third of vulvar cancers arise from a precursor caused by high-risk Human Papilloma Virus (hrHPV), called vulvar High-Grade Squamous Intra-Epithelial Lesion (vHSIL). The standardized incidence rate of vHSIL in Europe is estimated to be approximately 3.3 per 100,000 women years. In the Netherlands, an average of 300 women are newly diagnosed with vHSIL annually. Across Europe, there has been a consistent upward trend in vHSIL incidence over the past two decades, mirroring patterns observed in HPV-related malignancies [1]. The peak incidence of these precancerous vulvar lesions typically occurs between the ages of 35 and 40 [2]. Approximately 10% of women diagnosed with vHSIL, despite undergoing treatment, will progress to develop vulvar cancer within ten years after initial diagnosis. Recurrent vHSIL substantially increases the risk of malignancy [2].

Despite available treatments such as surgery, laser vaporization, and topical imiquimod, vHSIL recurrence rates remain high, affecting at least 30% of treated women within two years, regardless of treatment modality [2, 3]. Unfortunately, effective preventive strategies to address vHSIL recurrence are currently absent.

Promising empirical evidence suggests that HPV vaccination could reduce the risk of vHSIL recurrence. A retrospective secondary analysis of pooled data of two RCTs showed a significant reduction of 35% (irrespective of causal HPV type) to 64% (related to vaccine type) for recurrences of vHSIL and low-grade squamous intraepithelial lesion (LSIL) after adjuvant quadrivalent HPV vaccination [4]. Recently, a case-control study was published showing a reduction of 40% in recurrences after quadrivalent HPV vaccination; due to small groups, this reduction was not significant [5]. There is a notable absence of high-quality studies investigating adjuvant nonavalent vaccination, specifically in women treated for vHSIL.

We propose a prospective, double-blind, randomized controlled trial to evaluate the efficacy of adjuvant nonavalent HPV vaccination compared to placebo in reducing recurrence rates among women currently treated for vHSIL. Given that almost all HPV variants linked to vHSIL are covered by the nonavalent vaccine, this trial seeks to provide a novel preventive strategy for vHSIL recurrence [6–9].

This study aims to investigate the efficacy of nonavalent HPV vaccination versus placebo in preventing recurrence in women treated for vHSIL.

## Methods

### Study design

This is a randomized, multicenter, double-blinded, placebo-controlled trial involving 498 women diagnosed with vHSIL and scheduled for receiving treatment. Eligible participants will include women with histologically diagnosed vHSIL, both primary lesions and those with recurrence. Treatment follows current guidelines. Participants will be randomized to either receive adjuvant HPV vaccination or a placebo during treatment initiation, approximately two and six months into treatment (three dose regimen). All participants will undergo a two-year clinical follow-up as part of the trial. Throughout the study, participants will complete questionnaires, with Dutch participants optionally undergoing blood sampling to assess immune response three times. Participants may opt in to the blood sampling procedure, which is not obligatory for trial participation. Follow-up assessments adhere to current guidelines, and patients will receive standard treatment per the latest vHSIL guidelines. Long-term follow-up will examine vaccine efficacy after 5 and 10 years, along with the occurrence of vulvar malignancies (Figure 1 in Appendix).

### In- and exclusion criteria

Women aged eighteen or above with histologically proven vHSIL and planned for treatment are eligible for participation. Exclusion criteria include prior HPV vaccination, current invasive carcinoma or history of HPV-related genital carcinoma (cervix, anal, vulva), current pregnancy, allergy to vaccine components, patients with primary or secondary immunodeficiencies, including patients with HIV or on immunosuppressive medication, (see Tables 1 and 2 in the Appendix) and Human Immunodeficiency Virus (HIV) infection.

### Recruitment

Patients will be counseled about the study during consultations at the participating clinics. They will receive patient information along with an informed consent form, either on paper or digitally. If the histologic diagnosis is vHSIL and treatment is scheduled, the patient is eligible to enroll in the study.

### Study objectives and endpoints

The primary objective is to evaluate the efficacy of adjuvant nonavalent HPV vaccination in women who will undergo treatment for (histologically proven) vHSIL in preventing clinical recurrence of vHSIL up to 24 months.

The second objectives are:The effectiveness (complete remission) after treatment in patients receiving vaccination versus placebo at 6 and 12 months.Complete remission after treatment in patients receiving vaccination versus placebo at 6 and 12 months in primary episode (newly diagnosed) vHSIL versus recurrence.The effectiveness of adjuvant vaccination in different treatments of vHSIL (laser, imiquimod, excision) after 24 months.Additional treatment for vHSIL needed in the study period, and differences between the study groups.The effect of vaccination versus placebo on different hrHPV types (HPV type of primary and recurrence).The difference in immune response to HPV vaccination versus placebo vaccination. (We use HPV antibodies as a surrogate marker for immune response. Peripheral blood mononuclear cells (PBMCs) are bio banked for the possibility to measure in-depth cellular immune response at the molecular level at the end of the trial).Cost-effectiveness (IMTA Medical Consumption Questionnaire (iMCQ) and IMTA Productivity Cost Questionnaire (iPCQ) will be used).Quality of life (measured by Euroqol 5D-5L questionnaire) and sexual health (measured by Female Sexual Function Index, FSFI questionnaire) improved after vaccination compared to placebo.The effect of vaccination versus placebo on CIN/cervical cytology of the uterine Cervix.Long-term follow-up: The difference between HPV vaccination and placebo group in number of recurrences of vHSIL (5 and 10 years) and vulvar malignancies (2,5 and 10 years).

The primary endpoint is a difference in the number and percentage of patients with a clinical recurrence rate of vHSIL between HPV vaccination and placebo up to 24 months post-treatment.

The secondary endpoints are:Difference in the number and percentage of patients with a clinical recurrence rate of vHSIL between HPV vaccination and placebo at 6 and 12 months.Difference in the number and percentage of patients with a clinical recurrence rate of vHSIL between HPV vaccination and placebo at 6 and 12 months for primary vHSIL versus recurrent vHSIL.Difference in the number and percentage of patients with a clinical recurrence rate of vHSIL between the different treatment modalities.Difference in number and percentage for additional treatment necessary after primary treatment.Description and percentage of different hrHPV types. Percentage clearance of primary HPV type for vaccination versus placebo.Concentration of HPV antibodies and percentage of increase or decrease after vaccination.Is there a correlation between the number or percentage of recurrence? Is that different in primary versus recurrence episodes of vHSIL.Incremental cost-effectiveness ratio (ICER) describes the difference in costs and budget impact analysis.Description and change in numeric value and percentage in different score forms questionnaires. Percentage increase of decreased quality of life, sexual impact, and productivity impact.Difference in number and percentage of HPV types in cervical cytology and vHSIL before and after vaccination.Difference in number and percentage in the recurrence rate of vHSIL and vulvar cancer between HPV vaccination and placebo. Other HPV-related diseases known?

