### Detailed procedure

Patients with vulvar lesions are referred to the gynecologist according to their regular care. In the case of vHSIL, a biopsy will be taken for histological examination by a pathologist as part of regular care. At that time, potential participants will receive oral and written study information. In the case of histology-proven vHSIL participants will be invited for the screening visit.

In cases of uncertainty about whether a lesion is primary, residual, or recurrent, we have established an independent board of three experts on vulvar diseases to provide a definitive decision by consensus.

During the screening visit, routine cervical cytology (if not previously taken) and HPV status are obtained, along with visual examinations, including photo documentation to monitor lesion progression or regression.

At the follow-up visits, patients will undergo visual and physical examinations, with a preference for photo documentation of the vulva, to monitor any changes or recurrence of lesions or the development of new lesions. In case of suspicion of recurrence or a new lesion, a biopsy is taken. When it is not feasible to take a new biopsy, but new treatment is initiated, this is also considered a clinical recurrence. Quality-of-life questionnaires and immune response analysis will be performed, adhering to guideline-based care.

Recurrence is defined as any reappearance of vHSIL after six months from the start of treatment, while residual disease is defined as the presence of clinical suspicion and preferable histological conformation of vHSIL within six months from the start of the treatment.

In case of uncertainty regarding the histological diagnosis, an expert gynecological pathologist will review the slides digitally.

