### Data analysis

The primary outcome will assess the relative risk of vHSIL recurrence within 24 months, analyzing the efficacy of adjuvant nonavalent HPV vaccination using logistic regression methods adjusted for country of inclusion, treatment types, and primary versus recurrence vHSIL. A 95% confidence interval will be estimated for the odds ratio, with significance determined by a likelihood ratio test. *P*-values below 0.05 will be considered statistically significant.

Analysis of secondary endpoint(s) Secondary objectives 1, 2, 4, 9, and 10 will be analyzed similarly to the primary endpoint, using logistic regression methods adjusted for the stratification variables: country of inclusion, treatment types, and primary versus recurrence vHSIL. 95% Confidence intervals will be estimated for the odds ratios and significance will be determined using likelihood ratio tests. *P*-values below 0.05 will be considered statistically significant.

Secondary objectives where the effectiveness of vaccination is compared between different patient groups (secondary objectives 3 and 5) will be analyzed using logistic regression methods adjusted for stratification variables. 95% Confidence intervals will be estimated for the odds ratio, and significance will be determined using a likelihood ratio test. *P*-values below 0.05 will be considered statistically significant.

Secondary objective 6 will be analyzed using a linear regression model to determine the difference in log-transformed antibody levels at baseline and after placebo or vaccination and adjusted for stratification variables. The impact of change in antibody levels on the primary endpoint will be analyzed using a logistic regression model adjusted for stratification variables. 95% Confidence interval will be estimated for the coefficients, and significance will be determined using a likelihood ratio test. *P*-values below 0.05 will be considered statistically significant.

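### Secondary endpoints 1 and 2 measure clinical recurrence where the objectives ask about complete remission, and the recurrence definition leaves essentially nothing to count at month 6

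*Protocol article*

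**What the plan says.** All references are to the Methods of the protocol article.

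- **Objectives** (Study objectives and endpoints). Objective 1 is "The effectiveness (complete remission) after treatment in patients receiving vaccination versus placebo at 6 and 12 months". Objective 2 is the same outcome "at 6 and 12 months in primary episode (newly diagnosed) vHSIL versus recurrence".
- **Endpoints** (same section). Endpoint 1 is the difference in "clinical recurrence rate of vHSIL between HPV vaccination and placebo at 6 and 12 months". Endpoint 2 is the same variable "at 6 and 12 months for primary vHSIL versus recurrent vHSIL". Neither mentions remission, and neither says from what date the months are counted.
- **Definitions** (Detailed procedure). "Recurrence is defined as any reappearance of vHSIL after six months from the start of treatment". Residual disease is clinical suspicion, preferably with "histological conformation of vHSIL within six months from the start of the treatment". The same section also treats the start of a further treatment, where a biopsy cannot be taken, as a clinical recurrence. That rule carries no time limit.
- **Primary endpoint clock** (Study objectives and endpoints). The primary comparison is "between HPV vaccination and placebo up to 24 months post-treatment", which is a different origin from the one in the definition.
- **Analysis** (Data analysis). "Secondary objectives 1, 2, 4, 9, and 10 will be analyzed similarly to the primary endpoint", that is, by logistic regression adjusted for the stratification factors, with an odds ratio and a likelihood ratio test.

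**The concern.** An objective and its endpoint should describe the same quantity. Here the objective asks whether vaccination given around treatment helps the lesion clear, and the endpoint asks whether a lesion came back. At month 6 the mismatch is sharpest, because the protocol's own definition rules out recurrence up to that point.

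At stake are the first two secondary objectives, which are the ones that ask about clearance. An analyst who follows the endpoint list has a 6-month model with essentially nothing to fit and a 12-month model that answers another question. An analyst who follows the objectives fits remission, which is not a listed endpoint. The choice between the two should be settled in the text and not made during analysis.

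**Working it through.** The document states no figure for these endpoints, so the check is mainly one of setting the definitions side by side.

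**Step 1: month 6, clock at start of treatment.** A recurrence is countable only when its time from start of treatment exceeds 6 months. Recurrence by month 6 needs a time of at most 6 months. The two conditions do not overlap, so the window has length 0. With the planned 249 women per arm (Sample size calculations) that gives 0/249 against 0/249. With no events in either arm, both the model with and the model without the arm term fit perfectly: the likelihood ratio statistic is 0 and the odds ratio is not estimable. The same holds when the endpoint is split by first episode or recurrence.

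**Step 2: does recurrence stand in for remission?** The article does not define remission. I take it in the ordinary sense of no clinical or histological vHSIL at the time point. Four possible courses, dated from the start of treatment and leaving the re-treatment rule aside:

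| Course | Remission, month 6 | Recurrence by month 6 | Remission, month 12 | Recurrence by month 12 |
|---|---|---|---|---|
| Clear at month 5, stays clear | yes | no | yes | no |
| Never clears | no | no | no | no |
| Clear at month 3, lesion again at month 5, persists | no | no (residual) | no | no |
| Clear at month 5, vHSIL at month 9, still present at month 12 | yes | no | no | yes |

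The recurrence column at month 6 is constant. At month 12, the second and third women are scored as non-events, exactly like the first, who was cured. Recurrence is therefore not the complement of remission.

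**Step 3: is the 12-month recurrence endpoint empty too?** No. For illustration, assume a constant hazard over months 6 to 24 that yields the planning rates of 32% (placebo) and 19% (vaccine) by month 24. The 6 months from month 6 to month 12 are one third of those 18 months.

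- Placebo: 1 − 0.68^(6/18) = 0.1206; 249 × 0.1206 ≈ 30 events.
- Vaccine: 1 − 0.81^(6/18) = 0.0678; 249 × 0.0678 ≈ 17 events.

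**Step 4: what if month 6 is counted from the end of treatment?** The article gives no duration for a treatment course; I assume 4 to 16 weeks. Counting from the end of treatment then opens a window of weeks × 7/30.4375 months, that is 0.92 to 3.68 months. Under the same hazard the probability is 1 − (1 − p)^(window/18).

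| Assumed course | Window (months) | Placebo events /249 | Vaccine events /249 |
|---|---|---|---|
| 0 (one-day procedure) | 0 | 0 | 0 |
| 4 weeks | 0.92 | 4.9 | 2.7 |
| 8 weeks | 1.84 | 9.6 | 5.3 |
| 12 weeks | 2.76 | 14.3 | 7.9 |
| 16 weeks | 3.68 | 18.9 | 10.5 |

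These are upper figures for each duration, since they suppose that every woman has such a course. With a mix of treatments, whether an event can count at month 6 would depend on the treatment given.

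**The case against.** There are four answers to this point.

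1. **The planned model is attached to the objectives.** Data analysis assigns logistic regression to objectives 1 and 2, and those are about remission. Read literally, the regression is of remission by arm, which can be estimated. This stands. A reader might infer that the remission question has no analysis at all; the document does not support that. What is missing is an endpoint that matches the analysis.

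2. **Zero events is not certain.** The secondary endpoints give no time origin, the primary endpoint is timed from after treatment, and re-treatment without biopsy counts as clinical recurrence with no time limit. Some events could therefore enter by month 6. This also stands, so an unconditional claim of 0% against 0% goes too far. It does not rescue the endpoint: any events would come in through a different clock or through a rule that conflicts with the six-month definition in the same section.

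3. **A 12-month time point is meant to look at the early part of follow-up.** Correct. That it covers 6 of the 18 months in which recurrence can be counted is no defect. The fault at 12 months is only that recurrence does not measure remission.

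4. **A working definition of remission may sit in the full protocol or SAP.** It may, and its absence from an article is not held against the plan. But the article does state the objectives, the endpoints and the definition of recurrence, and these conflict as printed.

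**Conclusion.** The text is wrong as written for secondary endpoints 1 and 2. The objectives are about complete remission and the endpoints are about clinical recurrence. The 6-month recurrence endpoint has essentially no countable events, and hence no estimable odds ratio, provided that month 6 runs from the start of treatment and that the re-treatment rule is also confined to the period after month 6. If either condition fails, some events enter: on the assumed 4 to 16 week courses, at most about 5 to 19 in the placebo arm and 3 to 11 in the vaccine arm, and none for one-day procedures. The 12-month recurrence endpoint is estimable (about 30 against 17 events in the illustration), but women who never cleared are counted with those who were cured.

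A reader might go further and infer that the primary endpoint is also undermined. It is not voided by this point: recurrences between month 6 and month 24 remain countable. The sample size does not bear on the matter either.

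**What to change.** - Restate secondary endpoints 1 and 2 as complete remission, meaning no clinical or histological vHSIL, at 6 and at 12 months, by randomised arm and by first episode versus recurrence. State how a woman who recurs, is treated again and is clear by month 12 is classified.
- Delete recurrence at 6 months. If recurrence at 12 months is kept, label it as cumulative recurrence from month 6 to month 12.
- Give one time origin for all time points, reconciling the start-of-treatment clock in Detailed procedure with the after-treatment clock of the primary endpoint.
- Reconcile the untimed rule on re-treatment without biopsy with the six-month definition in the same section.
- Name the restated endpoints in Data analysis, so that the logistic model has an unambiguous outcome.

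The cost is wording in the protocol and the SAP. Data collection already provides for a visual and physical examination at each follow-up visit, with biopsy where recurrence is suspected, so no additional visits or patients are needed. The change should be made before unblinding.

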### Data collection

All data will be collected using an electronic Case Report Form (eCRF) and electronic questionnaires. Data from the eCRF and questionnaires will be collected and stored using Castor EDC. Sequential subject numbers will be assigned to enrolled participants in the study. Access to stored data will be restricted solely to the principal and coordinating investigators of each participating center.

Demographic and baseline disease characteristic data will be summarized for each treatment group and consist of age, parity, cervical cytology and HPV status, prior treatment for vHSIL, prior treatment for cervical HSIL, smoking, and co-morbidities in which we focus on auto-immune diseases and history of cancer.

At each follow-up visit, the following data will be collected: visual/physical examination and preferably photo documentation of the vulva. If there is any suspicion of recurrence of vHSIL, a biopsy will be taken for histology and HPV typing endpoint, cervical cytology, and if additional treatment will be started.

At the start of the study, after 6, 24, and 60 months, patients will be asked to fill out questionnaires.

